#### EQ-5D-5L

EQ-5D-5L questionnaires will be completed face to face at baseline and week 4. Postal/electronic versions will be administered at weeks 12 and 26 and at week 52 (where applicable, if wound is not healed). EQ-5D-5L is an accepted, five-item, generic, health-related quality of life measure including five items that can be combined to provide a single assessment of utility of life in a particular health state.^26^ The EQ-5D is a generic instrument (www.euroqol.org) and forms part of the National Institute for Health and Clinical Excellence (NICE) reference case for cost per QALY analysis.

#### Health resource use

Health resource use questionnaires will be completed at 4, 12 and 26 weeks and at week 52 (where applicable, if wound is not healed).

### Sample size

The sample size estimates are based on HEALS feasibility cohort data on time to healing and clinical and health economic considerations regarding an important reduction in number of days until complete healing. Assuming a median time to healing of 81 days in the SC arm^12^, a total of 396 randomised participants (198 per group) will provide 90% power for detecting a target effect size of 30% reduction in time to healing in the SC+CT group (57 days, HR=1.43), 2-sided log-rank test at 5% significance level and 10% attrition.

For the qualitative sub-study, it is expected that up to 25 patients will be identified to achieve a demographic spread and to achieve adequate depth and variety of data to sufficiently answer the study questions. We would aim for 1–2 patients from each recruitment site with representation from diverse sex and age groups.

### Statistical analysis

The statistical analysis will follow a predetermined, approved, version-controlled statistical analysis plan (SAP), and reporting will be in line with Consolidated Standards of Reporting Trials (CONSORT) standards.^27^ Statistical monitoring of safety data and underlying assumptions of the statistical design will be conducted and reported to the data monitoring and ethics committee (DMEC) according to an agreed DMEC Charter.

Baseline demographic data will be summarised to assess comparability between treatment arms using means and SD or medians and IQRs as appropriate for continuous variables, and numbers and percentages for binary and categorical variables. These same methods will be used to generate descriptive statistics where required.

#### Primary analysis of primary outcome measure

Primary analysis of the primary outcome measure, time to complete healing will be conducted on the intention-to-treat population using a multivariable Cox Proportional Hazards (PH) regression model adjusted for the minimisation factors post-excision wound area and wound depth; the potential for fitting centre as a random effect will be explored. Re-excision will be considered as a time-dependent covariate. Estimated HR will be presented with 95% CI and significance. Unadjusted Kaplan-Meier plots and estimates of survival functions (where ‘survival’ corresponds to *healing not observed*) and the stratified log-rank test statistic and its significance will be also reported. Should the PH assumption appear to be violated, an appropriate alternative analysis method will be used.

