### Randomisation

Randomisation will take place immediately postoperatively (in theatre or postoperative recovery area). 396 participants will be randomised in a 1:1 allocation ratio (198 per group) to SC or SC+CT stratifying by:

Centre.Immediate post-excision wound area (6.0 cm^2^ or less/more than 6.0 cm^2^ prior to any partial closure).^23^Wound depth (excision to fat/excision to fascia or periosteum).

Randomisation will be performed via a central, independent, secure 24-hour automated randomisation system provided by Leeds CTRU using a minimisation algorithm (including a random element) to ensure allocation concealment.

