#### Baseline assessment on the day of surgery/randomisation

Demographic information.Relevant medical history and clinical assessments.ABPI or Toe Pressure.CEAP.Factors affecting healing.Mobility.Questionnaire.EQ-5D-5L.In theatre.Post excision wound measurement – length, width, depth (excision to fat/excision to fascia or periosteum).Type of partial closure (purse string suture, side-to-side partial closure, eg, with pulley sutures or buried sutures, none).Post partial closure measurement (where applicable) – length and width.Following randomisationParticipant trial ID number.Randomisation allocation and details of intervention application.Date.Antibiotics.Related expected adverse and SAEs.

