#### Analysis of secondary outcome measures

*Wound infection measured by modified Bluebelle (WHQ*): a multivariable, random coefficients, repeated measures linear regression model will be fitted to modified Bluebelle WHQ score over time (until complete wound healing), including minimisation factors and randomised treatment. Centre, participant and participant-by-time interaction random effects will be explored. Time, treatment and treatment-by-time interaction will be fitted as fixed effects. An estimate for the magnitude of the treatment-by-time interaction and corresponding 2-sided 95% CI will be reported.*Number of days prescribed antibiotics for infection of the wound*: a multivariable Poisson regression model will be fitted to whether participant has been prescribed antibiotics over time, with an offset term for time at risk of being on antibiotics, including the minimisation factors and randomised treatment. Centre and participant random effects will be explored. An estimate for the difference in number of days where antibiotic prescribed and 95% CI will be reported.*Scar Quality (POSAS*): a multivariable linear regression model will be fitted to both participant and clinician POSAS scores, including the minimisation factors and randomised treatment. Centre random effects will be explored. Estimates for the differences in POSAS scores between the SC and SC+CT arms and 95% CIs will be reported.*Safety*: events including related complications and hospitalisations to healing (maximum 52 weeks post randomisation) will be summarised descriptively by treatment received.*Associations between partial closure method, post partial closure wound area and time to healing*: partial wound closure method and post-partial closure wound area will be included as additional covariates in the primary endpoint analysis model as described above. Wound area at baseline and 4 weeks post randomisation will be calculated using the elliptical method^34^ from maximum length and width measurements provided by site; time to complete wound healing will be determined as per the primary endpoint measure.

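### The primary Cox model commits to only two of the three minimisation factors and appears to use wound area as a two-level category, forgoing precision that baseline data already collected could give

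*Protocol article*

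**What the plan says.** The Randomisation section names three balancing factors: centre, immediate post-excision wound area (at most 6.0 cm² or above, before any partial closure) and wound depth (to fat, or to fascia or periosteum). Allocation is made "using a minimisation algorithm (including a random element) to ensure allocation concealment".

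Under Primary analysis of primary outcome measure, the Cox model is "adjusted for the minimisation factors post-excision wound area and wound depth; the potential for fitting centre as a random effect will be explored". A stratified log-rank test is also to be reported, without naming its strata. The coding of area in the Cox model is not given.

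The baseline list has length, width and depth after excision, and then an item beginning "Post partial closure measurement (where applicable", also with length and width. Both stand among the in-theatre items, ahead of those listed as following randomisation. Under Analysis of secondary outcome measures, "partial wound closure method and post-partial closure wound area will be included as additional covariates in the primary endpoint analysis model"; that section also says that wound area is calculated from length and width by the elliptical method.

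**The concern.** There are two separate matters.

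- **Centre.** It was used to balance the arms, yet the primary model does not commit to it. When an outcome depends on a balancing factor that the analysis omits, the standard error tends to be too large. In a Cox model, omitting a prognostic factor also pulls the treatment hazard ratio towards 1. An exploration step with no stated rule leaves two possible primary estimates. Centres may well differ here: standard care follows local policy, partial closure is at the surgeon's discretion, and the qualitative sampling table separates hospitals that routinely gave compression before the trial from those that did not.
- **Wound size.** Cutting area at 6.0 cm² before closure discards the gradient within each category, and it describes the wound before closure rather than the one left to heal. The plan already treats post-closure area as potentially prognostic, since its relationship to healing time is a secondary objective.

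At stake is the precision of the primary comparison, not its validity.

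**Working it through.** **1. The plan's own sample size.** The Sample size section gives these inputs: "Assuming a median time to healing of 81 days in the SC arm"; the target ("57 days, HR=1.43"); 90% power; two-sided 5% log-rank test; 10% attrition.

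- Target: 81 × 0.70 = 56.7 days, and 1/0.70 = 1.43.
- Schoenfeld events: 4 × (1.960 + 1.282)² / (ln 1.43)² = 42.03 / 0.1279 = 328.5, so 329.
- Participants: 329 / 0.925 / 0.90 = 395.2, so 396.

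The 0.925 is an assumption: the section gives no event probability, and 7.5% is the share unhealed at 6 months in the feasibility cohort (Patient burden). On that basis the stated 396 is reproduced. It rests on an unadjusted log-rank test.

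**2. What fuller adjustment would add.** The document gives no number of centres, centre variance or area effect, so all of these are assumed:

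- 396 participants, 20 centres, allocation balanced within centre × area category × depth;
- log hazard = ln(1.43) × treatment − slope × log post-closure area − 0.3 × deep wound + centre effect, with centre effects normal;
- centre SD 0, 0.2 or 0.4; slope 0.2, 0.5 or 0.8 per unit of log area;
- half the wounds partially closed; 10% attrition; follow-up of 26 to 52 weeks;
- 1,500 simulated trials per setting, with centre fitted as a Gaussian frailty.

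Power (%):

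| Centre SD | Slope | A: area category + depth | B: A + centre | C: continuous pre-closure area + depth + centre | D: continuous post-closure area + closure method + depth + centre | D − A |
|---|---|---|---|---|---|---|
| 0 | 0.2 | 92.1 | 92.2 | 92.4 | 92.8 | 0.7 |
| 0 | 0.5 | 90.4 | 90.2 | 91.8 | 93.1 | 2.7 |
| 0 | 0.8 | 86.3 | 86.4 | 90.2 | 92.7 | 6.4 |
| 0.2 | 0.2 | 90.9 | 91.5 | 91.7 | 91.9 | 1.0 |
| 0.2 | 0.5 | 89.0 | 89.9 | 91.0 | 91.7 | 2.7 |
| 0.2 | 0.8 | 85.1 | 85.5 | 89.9 | 92.4 | 7.3 |
| 0.4 | 0.2 | 87.4 | 91.1 | 91.1 | 91.7 | 4.3 |
| 0.4 | 0.5 | 84.5 | 88.9 | 90.3 | 91.5 | 7.0 |
| 0.4 | 0.8 | 80.0 | 85.0 | 88.7 | 91.3 | 11.3 |

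The Monte Carlo standard error of one figure near 90% is √(0.9 × 0.1 / 1500) = 0.8 points. Comparisons along a row use the same simulated trials.

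- **Centre alone (B − A):** between −0.2 and 0.9 points at SD 0 or 0.2, and 3.7 to 5.0 points at SD 0.4.
- **Attenuation (SD 0.4, slope 0.5):** mean hazard ratio 1.36 in A, 1.40 in B and 1.43 in D.
- **Type I error (same setting, true hazard ratio 1):** 4.4% in A, and 4.9% to 5.7% in the models with centre. The standard error is √(0.05 × 0.95 / 1500) = 0.6 points, so none departs clearly from 5%.

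**3. Stratifying by centre instead.** In a separate run with 15 or 30 centres this often cost power: for example, 93.1% fell to 88.3% with 30 centres and no centre effect.

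**Limits.** Healing was generated from post-closure area, which favours D over C by construction. D also includes closure method and omits the 6 cm² factor, so it approximates the model proposed below but is not identical to it.

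**The case against.** The strongest reply is that this is detail for the SAP. The article says that an approved SAP governs the analysis; the rule for a centre effect and the coding of a covariate are normally settled there, and exploring may mean only a check that the model converges. This stands in part. The document does not show that the model will be chosen after results are seen, and a reader should not infer that. Still, the article does more than stay silent: it commits to two factors and makes the third conditional without a rule.

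The two-level coding is an inference from the Randomisation and primary analysis sections read together. That also stands, and the point is worded accordingly.

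Post-closure area is already used in a secondary version of the model, and keeping the primary model to design factors is defensible. True, but the design factors include centre. No section states that closure is always measured before allocation is known; the order of the baseline list and randomisation immediately after surgery only make it likely. The fix depends on confirming it.

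A reader might infer from the figures below 90% that the trial is underpowered. They do not show that. The simulations set 1.43 as the hazard ratio conditional on covariates and centre, so the mean unadjusted hazard ratio was only 1.30 to 1.41. The plan's 1.43 comes from overall medians and an unadjusted test, which makes it a marginal effect. Only differences along a row are informative.

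**Conclusion.** The point holds as an available improvement. The primary model leaves out a firm commitment to one of its three minimisation factors and, on the natural reading, uses wound size in a coarse form although finer measurements are already recorded. The planned test is valid, the sample size reproduces, and the stated 90% power is not contradicted.

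The forgone gain was positive in all nine settings, from under 1 to about 11 power points and about 3 in the mid case (centre SD 0.2, slope 0.5), with some attenuation of the hazard ratio. These sizes rest wholly on assumed centre variation and area effect. If centres differ little and area is weakly prognostic, the gain is negligible. The gain from continuous area is the more consistent part once area is at least moderately prognostic; centre contributes materially only if centres differ substantially.

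**What to change.** Before unblinding, fix the primary Cox model as treatment, centre as a random effect (shared frailty), wound depth, the 6 cm² minimisation factor, and continuous log wound area at randomisation.

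- **Which area.** Use post-closure area, or post-excision area where there was no partial closure, provided that the measurement is confirmed as always taken before allocation is known. Otherwise use continuous post-excision area.
- **Fallback for centre.** If the frailty model does not converge, either omit centre or pool small centres by a rule written in advance; name one of these now. Do not stratify by unpooled centre, since that can cost power.
- **Closure method.** Keep it in the secondary model.
- **Missing area.** State a simple rule.

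The cost is wording in the protocol and SAP, with no new data. One small downside is that the hazard ratio becomes conditional on more covariates, so it should be reported as such beside the unadjusted Kaplan-Meier curves already planned.

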### Primary objective

To compare the time to HBSI from randomisation, between SC and SC+CT.

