### Post-randomisation re-excision of wound

In the event that a patient undergoes further surgery on their wound, they will continue in the trial unless the wound is no longer HBSI, for example, primary wound closure or the application of a skin flap or graft. Patients will be clinically withdrawn at this point and no further data collected.

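### On its natural reading, the primary Cox model conditions on re-excision after randomisation, so its hazard ratio is not the total effect of allocation; the size of the gap is unknown

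*Protocol article*

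**What the plan says.** The protocol article's *Primary objective* is "To compare the time to HBSI from randomisation, between SC and SC+CT". Under *Primary analysis of primary outcome measure*, the analysis is "conducted on the intention-to-treat population using a multivariable Cox Proportional Hazards (PH) regression model adjusted for the minimisation factors post-excision wound area and wound depth", with centre as a possible random effect. The next sentence is "Re-excision will be considered as a time-dependent covariate", and the one after it promises the estimated hazard ratio with its confidence interval. Unadjusted Kaplan-Meier estimates and a stratified log-rank test are to be reported as well.

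Two other sections fix the timing. Under *Randomisation*: "Randomisation will take place immediately postoperatively (in theatre or postoperative recovery area". Under *Post-randomisation re-excision of wound*, the rule on participants who have another operation on the wound is that "they will continue in the trial unless the wound is no longer HBSI". Where that operation ends secondary-intention healing, the rule is "Patients will be clinically withdrawn at this point and no further data collected".

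The *Sensitivity analyses* cover death as a competing risk, adherence and a parametric model aligned with the economic analysis. None is described as a Cox hazard ratio without re-excision. The secondary analysis of partial closure adds covariates to the primary model, so the re-excision term would carry over to it.

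**The concern.** Re-excision comes after allocation, in an open-label trial, and only to wounds that have not healed. Nothing in the article shows that it is independent of allocation. If compression changes how often it happens, part of the treatment effect runs through re-excision, and a model that holds re-excision status fixed removes that part. If wounds that heal slowly are also more likely to be re-excised, conditioning on re-excision makes the arms less comparable within each re-excision status.

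The case for adjusting is weak in either situation. If compression leaves re-excision unchanged, randomisation already protects the comparison. If compression changes it, the adjusted hazard ratio leaves out a real benefit or harm. What is at stake is the meaning of the headline estimate.

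**Working it through.** **1. The plan's own figures.** Inputs from *Sample size*: medians of 81 and 57 days, HR 1.43, two-sided 5% log-rank test, 90% power, 10% attrition, 396 participants.

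- Schoenfeld: 4 × (1.960 + 1.282)² / (ln 1.43)² = 4 × 10.51 / 0.1279 = 329 events.
- Freedman: 10.51 × (2.43 / 0.43)² = 336 events.
- Assumption for converting events to participants: exponential healing, 80% followed for 52 weeks and 20% uniformly over 26 to 52 weeks. Then 96.2% heal.
- N by Freedman: 336 / 0.962 = 350, and 350 / 0.9 = 389. By Schoenfeld: 380.
- Power at 396: 396 × 0.9 × 0.962 = 343 events; ½ × √343 × ln 1.43 − 1.960 = 1.352, which gives 91.2%.

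The stated 396 and 90% are reproduced closely. They rest on a log-rank comparison that does not involve re-excision.

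**2. Why the two hazard ratios differ.** Suppose re-excision multiplies the healing hazard by g. If a share p of the unhealed wounds in an arm has been re-excised, that arm's average healing hazard is its direct hazard × [1 − p(1 − g)]. The total-effect ratio is then roughly

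HR(total) ≈ HR(direct) × [1 − p(CT)(1 − g)] / [1 − p(SC)(1 − g)],

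whereas the model with the time-dependent covariate targets HR(direct). With g = 0.25 and direct HR 1.43:

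- 10% SC, 20% CT: 1.43 × 0.85 / 0.925 = 1.31.
- 20% SC, 10% CT: 1.43 × 0.925 / 0.85 = 1.56.

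This is crude, because p changes as wounds heal, so simulation is needed.

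**3. Simulation (150,000 per arm).** The re-excision risks and g are assumptions, since the article gives neither. The risks are intended values. Fewer re-excisions occur because some wounds heal first; an intended 20% becomes about 15% in SC.

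| Direct HR | Risk SC / CT | g | HR without re-excision | HR with re-excision | Shift |
|---|---|---|---|---|---|
| 1.43 | 5% / 5% | 0.5 | 1.423 | 1.432 | +0.009 |
| 1.43 | 20% / 20% | 0.25 | 1.353 | 1.421 | +0.068 |
| 1.43 | 20% / 10% | 0.5 | 1.489 | 1.429 | −0.060 |
| 1.43 | 20% / 10% | 0.25 | 1.517 | 1.431 | −0.086 |
| 1.43 | 10% / 20% | 0.5 | 1.336 | 1.429 | +0.093 |
| 1.43 | 10% / 20% | 0.25 | 1.230 | 1.412 | +0.182 |
| 1.00 | 10% / 10% | 0.25 | 1.000 | 1.000 | 0.000 |
| 1.00 | 10% / 20% | 0.25 | 0.902 | 0.999 | +0.097 |

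The adjusted hazard ratio stays near the direct effect throughout (1.41 to 1.44 when that is 1.43). The unadjusted one moves with re-excision. If slow healers are also made more prone to re-excision, the last row becomes 0.921 and 1.026.

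**4. A second set of assumptions.** Weibull healing with shape 1.6, control median 81 days, direct HR 1.43, re-excision at weeks 2 to 8, g = 0.37, 40,000 participants per scenario. Total and adjusted hazard ratios were 1.41 and 1.44 at 8% / 8%, 1.54 and 1.44 at 15% SC / 5% CT, and 1.25 and 1.41 at 5% SC / 15% CT. The pattern is the same.

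**The case against.** **The wording may not commit to the adjustment.** *Considered as* could mean that the term may be fitted, and the list of adjustment factors in the preceding sentence omits re-excision. This stands in part. The same paragraph uses *explored* for the optional centre effect, so *treated as* is the more natural reading. If the term is optional, the primary model is not settled, and the sentence needs correcting all the same.

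**Compression may not affect re-excision.** The specimen is removed before randomisation, and *Eligibility* (box 1) excludes patients suspected of a non-keratinocyte diagnosis or of needing further surgery. Re-excision prompted by histology would largely reflect facts fixed before allocation. This is a fair point, and it is why the size stays open: the shift is then 0.01 to 0.07 in the simulations, and with no effect on healing or re-excision both hazard ratios are 1.00. The larger gaps need a between-arm difference in re-excision for which the article offers no evidence.

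**A reader might infer that the trial would conceal a benefit or harm.** The documents do not support that. The Kaplan-Meier estimates and the stratified log-rank test do not condition on re-excision, and a log-rank test is the basis of the power calculation. What is missing is narrower: a covariate-adjusted hazard ratio free of re-excision.

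**A reader might also infer that intention to treat is breached.** The article uses the term for the analysis population, and the covariate excludes or reassigns nobody. It changes what the hazard ratio estimates.

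**Conclusion.** The point holds in a limited form. On the natural reading, the primary hazard ratio is an effect at a given re-excision status, which does not match the stated objective. Under the assumed re-excision risks (5% to 20%) and healing-hazard multipliers (0.5 or 0.25), it differs from the total effect by about 0.01 to 0.07 when compression leaves the risk of re-excision unchanged, and by up to about 0.18 when compression doubles it. Which case applies cannot be judged from the article. The concern that conditioning introduces selection is sound in principle but small in the null example examined: the adjusted hazard ratio moved from 1.00 to 1.03, and that case also assumed that compression doubles re-excision.

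It would be tempting to say that deleting the covariate gives a full treatment-policy effect. It does not, because data collection stops for participants whose further surgery ends in closure, flap or graft.

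**What to change.** - Define the primary Cox hazard ratio as adjusted for baseline factors only: post-excision wound area and wound depth, with centre handled as planned.
- State that re-excised participants still healing by secondary intention remain at risk, with time counted from randomisation, until healed or censored.
- Keep the time-dependent re-excision model as a labelled supplementary analysis, and say which version of the model the partial-closure analysis uses.
- Report re-excisions by arm.
- State that participants withdrawn after closure, flap or graft are censored at that point, that a full treatment-policy effect is therefore not recovered for them, and report their number by arm.

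The cost is a few sentences in the protocol and SAP. Further surgery on the wound is already recorded (*Follow-up phone calls/clinic visit* and *Week 4 clinic visit*), so no new data are needed. Sample size and power do not change. The article reports recruitment still in progress, so the wording can be settled before the final analysis.
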